**Methods:**

We will perform a multi-center cross-sectional interview study in Canada, USA, Norway and Finland. The study population will consist of 100 women with a history of lower extremity deep vein thrombosis (DVT) or pulmonary embolism (PE), and who are either pregnant, planning pregnancy, or may in the future consider pregnancy (women between 18 and 45 years). We will exclude individuals who are on full dose anticoagulation or thromboprophylaxis, who have undergone surgical sterilization, or whose partners have undergone vasectomy. We will determine each participant's willingness to receive LMWH prophylaxis during pregnancy through direct choice exercises based on real life and hypothetical scenarios, preference-elicitation using a visual analog scale (“feeling thermometer”), and a probability trade-off exercise. The primary outcome will be the minimum reduction (threshold) in VTE risk at which women change from declining to accepting LMWH prophylaxis. We will explore possible determinants of this choice, including educational attainment, the characteristics of the women’s prior VTE, and prior experience with LMWH. We will determine the utilities that women place on the burden of LMWH prophylaxis, pregnancy-related DVT, pregnancy-related PE and pregnancy-related hemorrhage. We will generate a “personalized decision analysis” using participants’ utilities and their personalized risk of recurrent VTE as inputs to a decision analytic model. We will compare the personalized decision analysis to the participant’s stated choice.

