**Figure 3 F3:**
[figure not shown]
Example of pictogram presentation for women considered at high risk of recurrent VTE during pregnancy.

For the VTE health state, we will instruct women to consider their previous venous thromboembolic event. Women with more than one event will consider their most recent episode. We will instruct women with previous experience in the use of prophylactic LMWH for longer than 2 weeks during pregnancy to consider their previous experience when making a decision. We have prepared a description of the experience of LMWH use throughout pregnancy for women without experience in the use of LMWH prophylaxis during pregnancy (Additional file 1: Appendix 1). To ensure clinical verisimilitude, clinicians with considerable experience in the use of LMWH in pregnant women prepared the description and experts in obstetrics and thromboembolism reviewed them.

After reviewing this information, we will ask participants to decide whether or not they are willing to take LMWH during their pregnancy (for those who are pregnant) or whether they would be willing to do so in a subsequent pregnancy. Women currently pregnant and those referred for consideration of prophylaxis with a future pregnancy will meet with their health care provider and may wish to discuss the information provided with other people (for example, family members, friends, family physician, midwife or obstetrician). We will record the final decision after these additional consultations.

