##### Visual analog scale (feeling thermometer)

Interviewers will determine the value patients place in relevant health states using a visual analog scale called the Feeling Thermometer (FT) [75]. When making ratings using the FT, women choose the score on the thermometer that represents the value they place on the health state they are evaluating. The FT is anchored at death (0) and full health (100). We will ask participants to consider (i) the health state of pregnancy with LMWH prophylaxis using the standard description or their previous experience (for those with two weeks or more of prophylactic LMWH during pregnancy), (ii) a pregnancy with their own most recent VTE experience, (iii) a standardized health state with a pregnancy-related DVT, (iv) a standardized health state with a pregnancy-related PE and (v) a standardized health state representing an obstetrical bleed (Additional file 1: Appendix I).

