Finally, we will perform a “personalized decision analysis” for each woman in the study. We will update a prior decision analytic model examining prophylactic LMWH in pregnant women with a history of prior VTE (Figure 4) [87], using each women’s visual analog scale utility assessments for the relevant outcomes of DVT in pregnancy, PE in pregnancy, obstetrical hemorrhage and the burden of LWMH prophylaxis in pregnancy. Given that the risk of heparin-induced thrombocytopenia (<0.1%) and heparin associated osteoporosis (<1%) are either not increased or minimally increased with prophylactic LMWH [65,68], we will not consider these health states in the decision analysis. We will place the health state utilities in the decision model for each woman’s current situation and the three hypothetical scenarios. We will compare the decision model’s results with the VTE threshold selected in the probability trade-off tasks.

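### The personalized decision model lists no input for the woman's own VTE, the event she is told to weigh in the real-life choice; a sensitivity run with that rating is needed

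*Protocol article*

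**What the plan says.** All references are to the protocol article.

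- **Real life scenario.** "For the VTE health state, we will instruct women to consider their previous venous thromboembolic event". The next sentence adds: "Women with more than one event will consider their most recent episode".
- **Visual analog scale (feeling thermometer).** Five states are rated. State (ii) is "a pregnancy with their own most recent VTE experience". States (iii) and (iv) are standardized descriptions of a pregnancy-related DVT and PE. The other two are LMWH prophylaxis and an obstetrical bleed. The Outcomes section lists the same five.
- **Analysis, Primary and secondary outcome(s), last paragraph.** The model takes each woman's ratings for the "relevant outcomes of DVT in pregnancy, PE in pregnancy, obstetrical hemorrhage and the burden of LWMH prophylaxis in pregnancy". It is run for her current situation and for the three hypothetical scenarios, and its results are compared with the trade-off threshold.
- **Abstract, Methods.** The same four states are named as the utilities to be determined for the decision analysis. The comparator is worded differently: "We will compare the personalized decision analysis to the" choice the participant stated.

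**The concern.** The Background presents direct choice and utility-based decision analysis as two routes to a patient-specific decision whose relative merit is unsettled, and the abstract makes the comparison between them a stated part of the study. That comparison is easiest to read when both sides value the same outcomes and differ only in method.

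For LMWH burden they do: a woman with previous experience uses it both when choosing and when rating, and otherwise she uses the standard description in both. For VTE they may not. The real-life choice rests on a remembered event, while the model appears to rest on scripted ones. A woman whose own clot was much milder or much worse than the script could disagree with her model result for that reason alone. The protocol itself expects the severity of the earlier VTE to matter, since it enters severity (severe, moderate, mild) as a determinant of both the threshold and the real-life choice.

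**Working it through.** **Step 1. Which VTE is valued where.**

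| Element | VTE event valued | Section |
|---|---|---|
| Real-life choice | Own, most recent | Real life scenario |
| Hypothetical choices | Not stated (own experience is mentioned only for LMWH burden) | Hypothetical scenarios |
| Feeling thermometer | Own most recent; standardized DVT; standardized PE, each rated separately | Visual analog scale |
| Trade-off threshold | Not stated; done after the thermometer | Probability trade-off; Direct choice exercises (order) |
| Decision model | DVT and PE; own VTE not listed | Primary and secondary outcome(s) |

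Five states are rated and four enter the model. The one left out is own VTE. The model paragraph does not use the word standardized. That follows because no other DVT or PE ratings are collected. The same paragraph explains why thrombocytopenia and osteoporosis are excluded, but says nothing about own VTE.

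**Step 2. Where the mismatch is explicit.** The own-VTE instruction appears only under the real-life scenario. It therefore bears directly on the current-situation run set against the stated choice, which is the abstract's comparator. For the trade-off threshold, which is the Analysis section's comparator, it is an inference that women still picture their own event.

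**Step 3. Can it change the model's answer?** The plan gives no figure to reproduce. As a one-period illustration that leaves out bleeding, let *B* be the rating of a pregnancy without VTE, *V* the VTE rating, *c* the LMWH burden in points and *r* the absolute risk reduction. The model favours LMWH if *r* × (*B* − *V*) > *c*. The threshold is *c* / (*B* − *V*), and the break-even VTE rating is *B* − *c* / *r*.

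- From Table 3, *r* = 4 − 1 = 3, 10 − 3 = 7 and 16 − 5 = 11 per 100. The value 7 per 100 is also the top of the high-risk range shown in the real-life exercise (Table 2).
- Assumed: *B* = 95, *c* = 2, own VTE 80, standardized VTE 50.

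| *r* per 100 | Gain, own VTE (× 15) | Gain, standardized (× 45) | Against burden of 2 |
|---|---|---|---|
| 3 | 0.45 | 1.35 | Both below: no reversal |
| 7 | 1.05 | 3.15 | Reversal |
| 11 | 1.65 | 4.95 | Reversal |

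The break-even rating at 7 per 100 is 95 − 2/0.07 = 66.4. The thresholds are 2/15 = 13.3 per 100 (own) and 2/45 = 4.4 per 100 (standardized), on a trade-off scale of 0 to 16. At the bottom of the high-risk real-life range, 70% of 5 is 3.5 per 100. The gains are then 0.035 × 15 = 0.53 and 0.035 × 45 = 1.58, both below 2, so there is no reversal.

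**Step 4. Range over the assumptions.** With *B* = 100 the break-even rating at 7 per 100 and *c* = 2 is 100 − 2/0.07 = 71.4. The gains at 7 per 100 become 0.07 × 20 = 1.4 (own) and 0.07 × 50 = 3.5 (standardized).

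| Burden *c* | Threshold, own (*c*/20) | Threshold, standardized (*c*/50) | Reversal at 7 per 100? |
|---|---|---|---|
| 2 | 10 per 100 | 4 per 100 | Yes |
| 3 | 15 per 100 | 6 per 100 | Yes |
| 5 | 25 per 100 | 10 per 100 | No |

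Reversal depends on the two ratings lying on opposite sides of the break-even value. Where they lie on the same side, the choice of rating does not alter the advice.

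**The case against.** A reader might infer that all the direct choices rest on the woman's own VTE, so that the whole model comparison is invalid. The documents do not support this. The Analysis section's comparator is the trade-off threshold, and the trade-off section does not say which VTE to picture. By the stated interview order, women have already rated the standardized DVT and PE when they reach the trade-off, so they may no longer have only their own event in mind. This limit stands. The counterweight is that the protocol checks consistency across the exercises, which makes most sense if one VTE state applies throughout.

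A reader might also infer that the own-VTE rating should replace the standardized ratings in the main model. That does not follow. The model has separate DVT and PE outcomes, while the own-VTE rating is one value for one past episode, and a recurrence need not repeat its type or severity. Standardized, type-specific states are a defensible choice. This objection stands.

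Further, the own-VTE rating is not discarded. It is summarised, and the utilities are related to the threshold by regression and correlation. That is true, but those analyses describe associations across women and do not show whether a woman's own model agrees with her own choice.

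Finally, the model's structure rests on a figure and a cited earlier model that are not shown, and the numerical example rests wholly on assumed ratings. Both points are accepted. However, the list of inputs is definite, and the abstract names the same four states.

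**Conclusion.** The point holds in a limited form. For the current-situation run set against the real-life choice, the choice is tied to the woman's own most recent VTE, and the model, by inference, to standardized DVT and PE. Discordance there mixes decision method with health-state description, and the plan has no run that separates them. For the trade-off threshold and the hypothetical scenarios, the same problem is possible but not established.

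The size cannot be derived from the documents. Under the assumed ratings, the model threshold moves by several VTE per 100 and its advice reverses in some settings but not in others. This shows that reversal can happen, not how often. The analysis concerned is a stated comparison, but it is neither the primary outcome nor one of the listed secondary outcomes. The change is a cheap improvement, not a correction on which the study depends.

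**What to change.** 1. Keep the planned run with the standardized DVT and PE ratings.
2. In the decision-analysis paragraph, prespecify a sensitivity run that substitutes the own-VTE rating for the event type the woman had. Whether that was DVT or PE is already recorded at interview. Leave the other type at its standardized rating.
3. Report agreement with both the real-life choice and the trade-off threshold, for both runs. This also reconciles the different comparators in the abstract and the Analysis section.
4. State which VTE women are to picture in the hypothetical scenarios and in the trade-off.

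The cost is one additional set of model runs per woman on data already collected, and a few sentences of text. No further ratings are needed. The limitation to state alongside is that one own-event rating cannot value both DVT and PE, so the added run supplements the standardized one and does not replace it.

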Providing thromboprophylaxis to those women at increased risk of thrombosis can potentially reduce pregnancy-related recurrent VTE. However, prophylaxis during pregnancy is problematic. Warfarin crosses the placenta and has the potential to cause teratogenicity and bleeding in the fetus [41-44]. Prophylactic LMWH does not cross the placenta [45] or increase the risk of serious adverse fetal outcomes [44-54], and does not appear to increase the risk of heparin-induced thrombocytopenia (<0.1%) or heparin-associated osteoporosis (<1%) [46,47,51,55-68]. However, prophylactic LMWH is expensive, inconvenient, uncomfortable to administer, may be associated with an increased risk of major obstetrical bleeding [46], and generally necessitates a planned delivery to permit epidural analgesia [46]. Additionally, women may perceive that LMWH creates an undesirable “medicalization” of their pregnancy.

A Cochrane systematic review [69] identified two randomized trials comparing heparin prophylaxis to placebo or no prophylaxis in pregnant women with prior VTE [11,70]. Both suffered from major methodological weaknesses including very small sample sizes. Current clinical guidelines are based primarily on the observational studies described above and indirect evidence suggesting that LMWH substantially decreases the risk of VTE by approximately 70% in a wide variety of clinical contexts [46,71].

In considering women’s choices of thromboprophylaxis during pregnancy, two considerations are of particular importance. First, treatment decisions during pregnancy have implications not only for the health of the mother, but also for the health of the fetus. Second, many women prefer to see pregnancy as a normal part of a healthy woman’s life, rather than as a medical condition. Additional considerations include the burden associated with the management: frequency and route of administration, pain, discomfort, and possible side effects of the medication, and the need, frequency and type of testing associated with a given regimen.

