Given that the desirable consequences do not clearly outweigh the undesirable consequences of prophylaxis (or vice versa), the values and preferences of pregnant women should be taken into consideration when making management decisions. Because individuals have different attitudes toward risk, the uncertainty of estimates for both the baseline risk of recurrent VTE and the effects of thromboprophylaxis makes the consideration of individual preferences even more important.

There are two fundamental approaches to “patient-specific” decision-making: (1) a holistic direct choice procedure and (2) utility elicitation from individual patients followed by “patient-specific” decision analysis. The relative merit of these approaches is open to question and few studies have addressed this issue [72]. In the “direct choice” methods, participants are presented with relevant health states and the probabilities associated with occurrence of those health states under alternative management strategies. The most rigorous and widely used experimental direct choice method is the probability trade-off or probabilistic version of the threshold technique and it involves determining the threshold benefit at which patients accept a treatment with fixed undesirable consequences or the threshold toxicity or adverse effects at which patients will decline a treatment with fixed benefit [73,74]. Investigators can also use other simpler direct choice methods (e.g. decision board) that provide complementary information and can ensure understanding of the probability trade-off.

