##### Real life scenario

We will initially present each woman with a decision board that will include the probabilities of developing VTE during pregnancy given the characteristics of her prior VTE (see below). This scenario will contain information similar to that received during standard clinical care but presented in a more systematic manner than that is typical in clinical practice.

For this real life exercise, we will have two potential scenarios. We will classify women as low or high risk of recurrence. We define low risk of recurrence as the absence of a known thrombophilia and prior VTE associated with a major transient risk factor within 8 weeks prior to their last event, and higher risk of recurrence as prior unprovoked VTE, VTE associated with a minor transient risk factor within 8 weeks prior to the event or any VTE in association with a known hypercoagulable state. (Table 1) We estimate that the risk of antepartum recurrence for women judged to be at lower risk lies between 0 and 5%, while that for higher risk women ranges between 5 and 10%. We will assume that prophylactic LMWH reduces the risk of antepartum recurrence by approximately 70% [71]. To ensure optimal understanding, we will present the risk of recurrence with and without LMWH prophylaxis in three different ways: table, bar chart and pictograph (Table 2 and Figures 2 and 3). 

**Table 2 T2:** Example of table presenting the risk of antepartum VTE recurrence for women considered at high risk of recurrent VTE during pregnancy

	**Without low molecular weight heparin use**	**With low molecular weight heparin use**
Probability of developing a blood clot during your pregnancy	5-10 in 100	1-3 in 100
Probability of NOT developing a blood clot during pregnancy	90-95 in 100	97-99 in 100

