##### Hypothetical scenarios

We will provide study participants with three standardized scenarios in which the baseline risk of recurrent VTE, with and without the use of LMWH (assuming a 70% relative risk reduction) [71], will be varied (Table 3). Interviewers will show each woman a decision board with pictograms representing a low, followed by a medium, then a high risk of recurrent VTE. Participants will express their willingness to use LMWH given the associated burden (either based on their own prior experience or the standardized description [Additional file 1: Appendix I]), and the absolute magnitude of VTE risk reduction associated with the varying VTE recurrence risks. 

**Table 3 T3:** Hypothetical scenarios with variable baseline risks of recurrent VTE and estimates of LMWH effectiveness

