##### Probability trade-off

Interviewers will undertake probability trade-off exercises with "ping-ponging" to determine participant thresholds for accepting LMWH prophylaxis [73,74]. We will use a scenario based on the absolute effects of LMWH versus no prophylaxis for prevention of recurrent VTE during nine months of pregnancy. The interviewer will systematically vary the risk of VTE with LMWH prophylaxis (alternating between high and low risks) to determine the minimum acceptable reduction in the risk of VTE with prophylaxis at which the participant would agree to initiate LMWH. Based on the 95% CI surrounding the incidence of antepartum VTE in high risk patients reported in the prospective cohort study [9], we estimate that the upper bound of risk of recurrent VTE is 16 out of 100 without prophylaxis. Therefore, we will set this risk fixed on one side of the flipchart and will start offering probabilities ranging from 16 fewer VTE events per 100 pregnancies (maximum absolute risk reduction) to 0 less VTE events (same VTE risk as no prophylaxis) on the other side of the chart.

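### The personalized decision model includes obstetrical hemorrhage, but the choices it is compared with are described with VTE probabilities only, so part of any difference may reflect information rather than preference

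*Protocol article*

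**What the plan says.** **Model side.** Under Primary and secondary outcome(s), the protocol article says an earlier decision model will be updated with each woman's feeling-thermometer ratings for the "relevant outcomes of DVT in pregnancy, PE in pregnancy, obstetrical hemorrhage and the burden of LWMH prophylaxis in pregnancy". Heparin-induced thrombocytopenia and osteoporosis are left out because LMWH raises them little or not at all. Hemorrhage is kept. The Background says LMWH "may be associated with an increased risk of major obstetrical bleeding". The Figure 4 caption says transition probabilities differ by strategy. No bleeding probability is given.

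**Choice side.**
- Real life scenario: women see "a decision board that will include the probabilities of developing VTE during pregnancy given the characteristics of her prior VTE". The Table 2 example has clot and no-clot rows only.
- Hypothetical scenarios: women weigh the LMWH burden against "the absolute magnitude of VTE risk reduction associated with the varying VTE recurrence risks". Table 3 has recurrence rows only.
- Probability trade-off: "We will use a scenario based on the absolute effects of LMWH versus no prophylaxis for prevention of recurrent VTE during nine months of pregnancy". Only the VTE risk on LMWH is varied, against a fixed 16 per 100.

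**Comparison.** The analysis section says: "We will compare the decision model’s results with the VTE threshold selected in the probability trade-off tasks". The Abstract says: "We will compare the personalized decision analysis to the participant’s stated choice".

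**Possible route for bleeding information.** A description of LMWH use, in an additional file that is not shown, was prepared for women without LMWH experience in pregnancy. Women with such experience draw on their own history. A standardized obstetrical bleed is rated on the feeling thermometer, which follows the real-life and hypothetical choices and precedes the trade-off.

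**The concern.** The Background describes direct-choice methods as presenting "relevant health states and the probabilities associated with occurrence of those health states under alternative management strategies". The analysis section counts hemorrhage among the relevant outcomes, yet no choice task is described as giving a bleeding probability by strategy. The two sides of the planned comparison may therefore rest on different sets of consequences.

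The Background also says that the relative merit of direct choice and of utility-based decision analysis is unsettled and little studied. This comparison is where the study can contribute to that question. If the model charges LMWH for bleeding and the woman was not asked to, the model will demand a larger VTE reduction than she did, even when her ratings and choices are fully coherent. That gap could be mistaken for a conflict between her values and her choice.

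**Working it through.** **1. Inputs from the article.** Relative risk reduction 70%; Table 3 baselines 4, 10 and 16 per 100; trade-off range 0 to 16 per 100.

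**2. The plan's own figures reproduce.** 4 × 0.3 = 1.2, shown as 1; 10 × 0.3 = 3; 16 × 0.3 = 4.8, shown as 5. The absolute reductions offered are 4 − 1 = 3, 10 − 3 = 7 and 16 − 5 = 11 per 100.

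**3. Threshold with and without bleeding.** This is a one-period, linear expected-utility simplification of the Markov model. Let B be the loss from the LMWH burden, V the loss from a VTE, H the loss from a bleed, and d the excess bleeding risk on LMWH.
- Woman weighing VTE against burden: T = B / V.
- Model with a bleeding term: T(model) = (B + d × H) / V.
- Shift = T(model) − T = d × (H / V).

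**4. Size of the shift.** The article gives neither d nor H/V, so both are assumed. Entries are VTE per 100.

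| d per 100 | H/V = 0.5 | H/V = 1 | H/V = 1.5 |
|---|---|---|---|
| 0 | 0 | 0 | 0 |
| 0.5 | 0.25 | 0.5 | 0.75 |
| 1 | 0.5 | 1 | 1.5 |
| 2 | 1 | 2 | 3 |

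**5. When a yes/no choice changes.** Model and woman part company on a board only if her threshold lies within the shift below the reduction offered.
- V = H = 0.40, B = 0.010: T = 0.010 / 0.40 = 2.5 per 100. The model gives 3.0, 3.5 and 4.5 at d = 0.5, 1 and 2 per 100. On the low-risk board (reduction 3) she accepts. The model declines at d = 1 and 2 but not at 0.5, counting a tie as acceptance. On the other two boards they agree throughout.
- Same V and H, B = 0.020: T = 5.0. The model gives 5.5, 6.0 and 7.0, and no board choice changes.

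**6. Share of women affected.** If thresholds were uniform on 0 to 16 (an assumption), the share changing on one board is shift / 16: 0.5/16 = 3.1%, 1/16 = 6.25%, 2/16 = 12.5%, 3/16 = 18.75%. The numeric threshold differs whenever d and H are both above zero, even when no yes/no choice changes.

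**7. If the LMWH description does cover bleeding.** Suppose a woman's LMWH rating already includes it, so her burden loss is B + d × H. Her stated threshold is then (B + d × H) / V. A model with a separate bleeding term gives (B + d × H + d × H) / V. The gap is again d × (H / V), this time from counting bleeding twice.

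**The case against.** A reader might infer that the boards show VTE probabilities and nothing else, and that coherent women will be scored as disagreeing with their own model. The article does not support that. The real-life board is said to include VTE probabilities, which does not exclude other content, and its information is meant to resemble usual clinical care. Table 2 is an example. The Background counts possible side effects among the burdens of management, and the hypothetical choices are made in light of that burden. The scripts, figures and LMWH description are not shown. Varying one benefit while harms are held constant is also how the article defines the trade-off, so it does not show that the harms were withheld.

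Timing also weakens the strong reading. Women rate the described bleed before the trade-off, whose threshold is the comparator named in the analysis section. Pregnant and referred women consult their provider before their real-life decision is recorded. No agreement score or tolerance is defined, and the excess bleeding risk may be zero.

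These objections stand against the strong reading, but they leave a narrower point. No choice task is described as giving bleeding probabilities by strategy. Rating a bleed conveys how bad it is, not how often it occurs with and without LMWH. The LMWH description was prepared for inexperienced women only, and if it mentions bleeding, double counting becomes possible. Keeping hemorrhage while dropping harms that LMWH hardly raises makes an excess-bleeding term in the model a fair inference, though not a stated fact.

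**Conclusion.** The point holds in limited form and is minor. As described, the model and the choice tasks need not carry the same consequences, so a difference between them can mix preference with information or with double counting. The shift is 0 to 3 VTE per 100 for an assumed excess bleeding risk of 0 to 2 per 100 and a loss ratio of 0.5 to 1.5. It is exactly zero if the model gives LMWH no excess bleeding. The shares in the working also need uniform thresholds and women who do not weigh bleeding on their own account.

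A reader might go further and conclude that the primary VTE threshold is too low. The documents do not support this. The primary outcome is defined as the switching point in the exercise, and its mean, confidence interval and sample size of 100 do not depend on the model. The issue is confined to the decision-analysis comparison, which is not listed among the primary or secondary outcomes.

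**What to change.** In the personalized decision analysis paragraph, state that each woman's model will be run twice for the comparison with her stated choice and VTE threshold:
1. with the bleeding probability equal in the two strategies;
2. with the excess-bleeding term, giving the value used.

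Report both, and state that the difference between the runs is not evidence of inconsistent preference. Two runs are needed because the right match depends on what a woman took into account. The first suits choices made without bleeding information, and also the case where the LMWH rating already contains bleeding. The second suits women who weighed bleeding in the choice but not in that rating.

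The cost is a sentence or two of text and one additional model run on ratings already planned. No change to the boards is required.
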